## Ethics and dissemination

### Ethics approval

The trial will be conducted according to the guidelines laid down in the Declaration of Helsinki, the guidelines of the Ethics Review Panel (ERP) of the University of Luxembourg and the European Union General Data Protection Regulation (GDPR). The study design was approved by the ERP on 26 June 2020 (ERP 20-029 SHER). In case of protocol modifications, prior approval of the University’s Ethics Review Panel will be sought and communicated to all parties concerned (trial participants and trial registries).

The study is registered on ClinicalTrials.gov (NCT04792177); all necessary information according to the WHO recommendations is provided (Table 2).

**Table 2 Tab2:** WHO trial registration dataset

Data category	Information
1. Primary registry and trial identifying number	ClinicalTrials.gov NCT04792177
2. Date of registration in primary registry	29 January 2021
3. Secondary identifying numbers	–
4. Source(s) of monetary or material support	University of Luxembourg, Luxembourg National Research Fund
5. Primary sponsor	University of Luxembourg
6. Secondary sponsor(s)	FNR—Luxembourg National Research Fund
7. Contact for public queries	[name] [name], University of Luxembourg, Esch-sur-Alzette, Luxembourg; email: [contact]
8. Contact for scientific queries	[name] [name], University of Luxembourg, Esch-sur-Alzette, Luxembourg; email: [contact] [name], University of Linköping, Linköping, Sweden; email: [contact] [name], University of Lausanne, Lausanne, Switzerland; email: [contact] [name], Dipl. Psych., PhD, University of Luxembourg, Esch-sur-Alzette, Luxembourg; email: [contact]
9. Public title	Internet-based emotion regulation intervention for sexual health
10. Scientific title	Internet-based emotion regulation intervention for sexual health (SHER 2)
11. Health condition(s) or problem(s) studied	Sexual health, mental health, emotion regulation
12. Intervention(s)	*Emotion regulation skills training*: The intervention will consist in an online emotion-regulation skills training for individuals with sexual problems. It will last for 8 weeks, encompassing psycho-educational and emotion-regulation skills components. Every week participants will gain access to a different intervention module of the training, containing videos, presentation slides, written support material, and a recommendation of activities to be completed until the following week of training. Participants are expected to dedicate 30 min to 1 h per week to complete each module.
13. Key inclusion and exclusion criteria	*Inclusion criteria for participants:* 1. Between 18 and 65 years of age. 2. Fluent in Brazilian Portuguese. 3. Self-reported sexual problems, assessed in men by a score of < 21 on the International Index Erectile Function (IIEF) and in women by a score of < 26 on the Female Sexual Function Index (FSFI). 4. In a stable relationship for at least the preceding 3 months. *Exclusion criteria for participants:* 1. Medical conditions that can interfere with the outcomes of the intervention, e.g., diabetes, cancer, and cardiovascular problems. 2. Ongoing psychotherapy.
14. Study type	Type: interventional Study design: - Allocation: randomized. - Intervention model: parallel assignment. - Masking: none (open label) - Primary purpose: treatment
15. Date of first enrolment	10 March 2021
16. Sample size	102
17. Recruitment status	Enrolling
18. Primary outcome(s)	- Change in Female Sexual Function Index (FSFI) at 6 months (time frame: baseline, 2 months after baseline (end of intervention), and 8 months after baseline (follow-up)). - Change in International Index of Erectile Function (IIEF) at 6 months (time frame: baseline, 2 months after baseline (end of intervention), and 8 months after baseline (follow-up)). - Change in Sexual Quotient (QS) at 6 months (time frame: baseline, 2 months after baseline (end of intervention), and 8 months after baseline (follow-up)).
19. Key secondary outcome(s)	Change in Sexual Modes Questionnaire (SMQ)—Automatic Thoughts subscale (time frame: baseline, 2 months after baseline (end of intervention), and 8 months after baseline (follow-up). Change in Sexual Self-Schema Scale (SSSS) (time frame: baseline, 2 months after baseline (end of intervention), and 8 months after baseline (follow-up)). Change in Patient Health Questionnaire-9 (PHQ-9) (time frame: baseline, 2 months after baseline (end of intervention), and 8 months after baseline (follow-up)). Change in General Anxiety Disorder—7 (GAD-7) (time frame: baseline, 2 months after baseline (end of intervention), and 8 months after baseline (follow-up)). Change in the Difficulties in Emotion Regulation Scale (DERS) (time frame: baseline, 2 months after baseline (end of intervention), and 8 months after baseline (follow-up)).
20. Ethics review	Ethical approval has been obtained from the Ethics Review Panel of the University of Luxembourg (ERP 20-029 SHER).
21. Completion date	30.04.2022 (anticipated)
22. Summary results	n/a
23. IPD sharing statement	Undecided

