### Sample size

Considering the number of variables of the study (with a power of .80 or greater and with a significance level set at *α* = .05), the minimum sample size needed to find meaningful differences in sexual health is 102 participants (51 in the intervention and 51 the control group [26]). Considering gender differences, we will aim to obtain twice this sample size (*N* = 204), i.e., 102 participants per gender.

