#### Outcomes

*Primary outcome*
Improvements in self-reported sexual health from baseline to 6-month follow-up.*Secondary outcomes*Emotion regulation improvement (from baseline to 6-month follow-up).Reduction in automatic thoughts during sexual activity (from baseline to 6-month follow-up).Reduction in anxiety scores (from baseline to 6-month follow-up).Reduction in depression scores (from baseline to 6-month follow-up).Improvement in sexual self-schema (from baseline to 6-month follow-up).

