#### Sexual health

Sexual health will be assessed using four questionnaires, two of which concern self-perception as a sexual person, thoughts, and emotions during sexual activity and two questionnaires on sexual function.

Female participants will be asked to complete the Female Sexual Function Index (FSFI [27]) and the Sexual Quotient- female version (SQ-f [28]), while male participants will be asked to answer the International Index of Erectile Function (IIEF [29]) and the Sexual Quotient- male version (SQ-m [30]).

A) *Female Sexual Function Index (FSFI)* [27]: this is a 19-item questionnaire for the assessment of sexual functioning in women in domains of sexual functioning (e.g., sexual arousal, orgasm, satisfaction, pain). Answers are provided using a 5-point Likert scale. Hentschel et al. [31] translated and validated the he FSFI into Portuguese, showing good internal consistency both for the evaluation of the total scale (*α* = .92) and for specific domains (desire = .67; excitation = .80; lubrication = .89; orgasm = .87; satisfaction = .85; pain = .86).

B) *International Index of Erectile Function (IIEF)* [29]. The *IIEF* is 15-item, self-administered questionnaire for assessing sexual functioning in men. Answers are given on a 6-point Likert scale. The *IIEF* encompasses five different domains of sexual functioning: erectile function, orgasm function, sexual desire, intercourse satisfaction, and overall satisfaction. Ferraz and Cicconelli [32] translated and adapted the scale to Brazilian Portuguese. Its psychometric properties were assessed by Gonzáles et al. [33], showing good internal consistency for both the full scale (*α* = .89) and the specific domains (erectile function = .86; orgasmic function = .63; sexual desire = .77; sexual satisfaction = .60; general satisfaction = .73).

C) *Sexual Modes Questionnaire (SMQ)* – Automatic Thoughts subscale [34]. This self-report scale consists of 30 items in the male version and 33 items in the female version. Respondents are asked to rate the frequency (from 1 [never] to 5 [always]) with which they have experienced specific automatic thoughts during sexual activity. The psychometric properties of the Brazilian adapted version were evaluated by Lucena [35], with an internal consistency of *α* = .92 and retest reliability of *r* = .8 (*p* < .05) for the female version and *α* = .95 and *r* = .82 (*p* < .05) for internal consistency and reliability, respectively, for the male version.

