D) *Sexual Quotient (QS)* [28, 30]. The *QS* is a brief and comprehensive tool composed of 10-questions, which are answered on a scale from 0 (never) to 5 (always). It addresses general sexual function and stages of the sexual response cycle (desire, arousal, orgasm) and sexual satisfaction. The female version showed excellent internal consistency, both for the questionnaire as a whole (*α* = .98) and for each of its domains (all with *α* ≥ .9) [28]. The male version showed satisfactory internal consistency for the questionnaire as a whole (*α* = .6) and for the separate domains (all with *α* ≥ .6).

E) *Sexual Self-Schema Scale (SSSS)*. Originally developed by Hill [36], the Brazilian version of the *SSSS* consists of 30 items assessing respondents’ perception of themselves as a sexual person compared to others of the same gender and age. Answers are provided using a 5-point Likert scale ranging from 1 (not at all descriptive of me) to 5 (very much descriptive of me). It has good test-retest reliability (*r* = .6, *p* < .05) and internal consistency (scale total Cronbach's alpha of .8, ranging from .61 to .85 for the three factors [35]).

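### The primary outcome is stated inconsistently: one section puts two secondary measures inside sexual health, and the registered set has several unranked primary scores at a .05 significance level

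*Protocol article*

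**What the plan says.** All references are to the protocol article.

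- **Abstract, Methods and analysis:** sexual function and satisfaction are primary; sexual self-perception is secondary. No instrument is named.
- **Aim:** sexual self-perception, defined as self-schema plus automatic thoughts, belongs to the second aim, as a possible mediator.
- **Outcomes:** the primary outcome is "Improvements in self-reported sexual health from baseline to 6-month follow-up". Automatic thoughts and sexual self-schema are listed as secondary.
- **Measurements, Sexual health:** "Sexual health will be assessed using four questionnaires, two of which concern self-perception as a sexual person, thoughts, and emotions during sexual activity"; the other two concern sexual function. The SMQ and SSSS are described under this heading. Women complete the FSFI and the female QS, men the IIEF and the male QS.
- **Data analysis:** sexual health and sexual self-perception are named as separate domains. The model is a repeated-measures ANOVA with time and group, and no sex factor is mentioned.
- **Table 2, item 18:** FSFI, IIEF and QS ("Change in Sexual Quotient (QS) at 6 months") are primary, with no order among them.
- **Table 2, item 19:** the SMQ subscale and "Change in Sexual Self-Schema Scale (SSSS") are secondary.
- **Sample size:** "significance level set at *α* = .05", "with a power of .80 or greater", giving "102 participants (51 in the intervention and 51 the control group"), doubled to 204 so that each gender has 102.

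**The concern.** Two separate things go wrong.

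First, the Outcomes and Sexual health sections read together place automatic thoughts and self-schema inside the primary outcome, while other parts of the article place them outside it. These statements cannot all hold. The distinction matters because the trial is open label with a waitlist control and self-reported outcomes, and the week 4 module works directly on automatic thoughts about sexuality. A change on the SMQ would be a change on something the training targets, not a change in sexual function. The sample size is also justified by differences in sexual health, the term whose content is in dispute.

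Second, even if Table 2 alone governs, every participant contributes two primary scores and the article does not say which one decides. A reader cannot tell what result would count as success on the first aim. If any one positive score is enough, the stated 5% level does not describe the error rate of the claim.

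**Working it through.** **1. The plan's own figure.** No effect size is given, so 102 cannot be reproduced from the article's inputs alone. Solving backwards with a two-sample t test at alpha .05 and power .80:
- two-sided, 51 per arm detects d = 0.56 (power 80.0%);
- one-sided, d = 0.50 needs exactly 51 per arm (power 80.6%);
- two-sided, d = 0.50 would need 64 per arm.

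I take 51 per arm within each sex, as the Sample size section plans. (Table 2 item 16 gives 102 in total, which also needs reconciling.)

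**2. Where each measure is placed.**

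| Measure | Outcomes + Sexual health sections | Aim / Outcomes list / Data analysis | Table 2 |
|---|---|---|---|
| FSFI, IIEF | primary | sexual health | primary |
| QS | primary | sexual health | primary |
| SMQ thoughts | inside the primary construct | secondary, or separate domain | secondary |
| SSSS | inside the primary construct | secondary, or separate domain | secondary |

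The conflict lies in the SMQ and SSSS rows, and its source is the opening sentence of the Sexual health section.

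**3. Number of primary tests under Table 2.** Women have FSFI and QS; men have IIEF and QS. Tested within sex, that is four tests. Per-gender sizing, separate randomization lists and sex-specific QS versions support this reading, but the article does not state it. With QS pooled over the sexes there are three.

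**4. Chance of at least one significant primary test when the intervention has no effect.** Each test is at 5%. The within-sex correlation r between the two scores is an assumption, taken from 0 to 0.9. The sexes are independent samples.

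*Four tests, two-sided.* Let p be the chance that at least one of the two tests within a sex has |Z| > 1.96 (bivariate normal). The total is 1 − (1 − p)².
- r = 0: p = .0975, total = 1 − .95⁴ = 18.5%
- r = 0.5: p = .0907, total 17.3%
- r = 0.7: p = .0835, total 16.0%
- r = 0.9: p = .0704, total 13.6%

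*Three tests, QS pooled.* The pooled QS statistic correlates r/√2 with each sex-specific score. Independence gives 1 − .95³ = 14.3%. Simulation gives 13.6% at r = 0.5, 13.0% at 0.7 and 12.1% at 0.9.

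*Only favourable results of two-sided tests count* (2.5% per test).
- Four tests: 1 − .975⁴ = 9.6% at r = 0; 8.9% at 0.5; 8.2% at 0.7; 6.9% at 0.9.
- Three tests: 1 − .975³ = 7.3% at r = 0, falling to 6.1% at 0.9.

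On this reading a single test would carry 2.5%, so that is the fair comparison.

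**5. What the remedies do.** One score per sex, each left at 5%, still gives 1 − .95² = 9.75%. Starting at .025 each gives 1 − .975² = 4.94%. At 51 per arm, two-sided with 80% power, the detectable d is 0.560 at alpha .05, 0.618 at .025 (Holm's first step for two tests) and 0.672 at .0125 (first step for four tests). At d = 0.56, power is 80.0%, 70.9% and 61.3% respectively.

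**The case against.** **The self-perception scales are plainly secondary.** Several places in the article say so, and only one sentence says otherwise. This stands to a large extent. A reader might infer that the team intends to claim the primary aim on the SMQ or SSSS; the documents as a whole do not support that. What remains is a contradiction that a sentence can remove.

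**A construct in one section and its instruments in another are nested, not conflicting.** That is fair for the Abstract, Outcomes and Table 2, since QS is described as covering both function and satisfaction. It does not rescue the Sexual health section, and it does not say which instrument decides.

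**A multiplicity rule may sit in an analysis plan that is not shown.** Correct, and its absence is not the point here. Which measure is primary is protocol and registry content, and it is stated inconsistently.

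**The error rate is conditional.** A reader might infer a fixed false-positive chance of about one in six. That needs QS tested within each sex, any single positive test counting as success, r near 0.6, and either direction counting (or one-sided 5% tests). The article states none of these. If all scores had to be positive, there would be no inflation, only a loss of power.

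**Is QS the noisier scale?** A reader might infer so from the men, where alpha is .6 ("The male version showed satisfactory internal consistency for the questionnaire as a whole") against .89 for the IIEF. In women the order reverses: .98 for QS against .92 for the FSFI. Reliability therefore does not justify demoting QS in both sexes, and the point does not rest on it.

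**Conclusion.** The point holds as an inconsistency in the primary outcome, together with an unranked set of registered primary scores. The inconsistency follows from the article's text and needs no assumption.

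The inflation is conditional on one positive test being enough. It is then 13.6-18.5% with four tests, 12.1-14.3% with three, and 6.1-9.6% across both counts if only favourable two-sided results are taken. Every variant exceeds 5%, but the size depends on an assumed correlation, on sidedness and on how QS is analysed, so it should be quoted as a range. It matters enough to settle before any outcome analysis, because the article does not fix what result would establish efficacy.

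**What to change.** 1. Correct the opening of the Sexual health section: the SMQ subscale and SSSS measure sexual self-perception and are not part of the primary outcome. This brings it into line with the Aim, Outcomes and Data analysis sections and Table 2 item 19.
2. Before any outcome analysis, name one deciding score per sex at the 6-month follow-up, stated as 8 months after baseline: the FSFI total for women and the IIEF full-scale total for men, with QS secondary. Use the same wording in the Abstract, Outcomes and Table 2 item 18. Alternatively, keep QS primary and apply Holm across all registered primary tests.
3. State whether success in either sex supports the efficacy claim. If so, apply Holm across the two sexes.

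**Cost.** No new data or questionnaires. Table 2 shows the trial enrolling, and the article requires prior ethics approval for modifications, so this means an approved amendment and a registry update, not only an edit. At 51 per arm the first-step detectable d rises from about 0.56 to 0.62 (power at d = 0.56 falls from 80.0% to 70.9% at that step); once one sex succeeds, the other is tested at the full 5%. Keeping QS primary with four tests raises the first-step figure to about 0.67.

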### Dissemination plan

Study findings will be disseminated through peer-reviewed publications, conference presentations, posters, and social media channels. The research findings will provide important information concerning the efficacy of an Internet-based emotion-regulation intervention for sexual health. The outcomes of the study have the potential to establish the evidence-base for an Internet-based emotion-regulation intervention for sexual dysfunctions. The results will also contribute to the identification of the processes involved in the effects of improved emotion regulation skills on depressive and anxiety symptoms, and on sexual self-schema.

### Comment

To our knowledge, this will be the first Internet-based emotion regulation intervention to promote sexual health.

## Data Availability

After completion of the study, the results will be disseminated to the study participants and the general public via submission for publication in international peer-reviewed journals and for presentation at national and international conferences.
